**Adverse Events**

An adverse event (AE) is any untoward medical occurrence in a clinical investigation subject administered a medicinal product and which does not necessarily have a causal relationship with this treatment. An AE can therefore be any unfavorable and unintended sign, symptom, or disease temporally associated with the use of a medicinal product, whether or not considered related to the medicinal product. Pre-existing events, which increase in severity or change in nature during or as a consequence of use of a medicinal product in human clinical trials, will also be considered AEs.

Any medical condition or clinically significant laboratory abnormality with an onset date before the screening visit and not related to study procedures is considered to be pre-existing, and should be documented in the case report form.

Any AE (i.e., a new event or an exacerbation of a pre-existing condition) with an onset date after the screening visit up to the last day on study (including the follow-up, off study medication period of the study), should be recorded as an AE on the appropriate CRF page(s).

An AE does not include:

- Medical or surgical procedures (e.g. surgery, Endoscopy, tooth extraction, transfusion); the condition that leads to the procedure are an adverse event.
- Pre-existing diseases or conditions or laboratory abnormalities present or detected prior to the screening visit that does not worsen.
- Situations where an untoward medical occurrence has not occurred (e.g. hospitalization for elective surgery, social and/or convenience admissions).
- Overdose of either study drug or concomitant medication without any signs or symptoms unless the subject is hospitalized for observation.

***Assessment of Adverse Events***

All AEs will be assessed by the investigator and recorded on the appropriate CRF page, including the date of onset and resolution, severity, relationship to study drug or study procedures, outcome and action taken with study medication.

The relationship to study drug therapy or study procedures should be assessed using the following definitions:

**No**: Evidence exists that the adverse event has an etiology other than the study drug or study procedures (e.g. pre-existing condition, underlying disease, intercurrent illness, or concomitant medication).

**Yes**: A temporal relationship exists between the event onset and administration of the study drug or between the event and the study procedures. It cannot be readily explained by the subject’s clinical state or concomitant therapies and, in the case of the study drug, appears with some degree of certainty to be related based on the known therapeutic and pharmacologic actions or adverse event profile of the study drug. In case of cessation or reduction of the dose, the event abates or resolves and reappears upon re-challenge. It should be emphasized that ineffective treatment should not be considered as causally related in the context of adverse event reporting.

These criteria in addition to good clinical judgment should be used as a guide for determining the causal assessment. If it is felt that the event is not related to study drug therapy, then an alternative explanation should be provided.

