**Exclusion criteria**

Patients will be excluded if they will have one of the following criteria:

- Dynamic neurologic improvement or worsening during the last month
- Had been treated with HBOT for any other reason prior to their inclusion
- Have any other indication for HBOT;
- Chest pathology incompatible with pressure changes;
- Inner ear disease;
- Patients suffering from claustrophobia;
- Inability to sign written informed consent.
- Smoking patients were not allowed to smoke during the study and if they could not comply with this demand they were excluded.
- Inability to sign informed consent

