***Study protocol***

After signing the informed consent, patients were randomized in 1:1 manner into the treated or the control-cross group. After the randomization, patients were invited for baseline evaluation that included full review of their medical status and complete physical examination. All patients had baseline CT scan. After their inclusion patients were randomized to two groups: a treated group and a cross group. All patients had evaluation of their neurologic functions by physical examination, ability to perform activities of daily living, quality of life and brain functional imaging (rCBF-SPECT scan). The patients in the treated group were evaluated twice – at baseline and after 2 months of HBOT treatment. The patients of the cross group were evaluated three times – at baseline, after a 2 month control period of no treatment and after a consequent 2 month period of HBOT treatment. We emphasize that the study was a cross-over trial and patients in the cross group received HBOT treatment after their second evaluation and had a third neurological evaluation after the cross, when they have completed their HBOT.

The following HBOT treatment protocol was practice: The patient were treated 40 times (each treatment session was given on a separate day) distributed over two months (five days a week). Each session was for 90 minutes in 100% oxygen atmosphere and at pressure of 2 ATA.

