**Brain functional Imaging SPECT imaging and Analysis**

Single photon emission computed tomography (SPECT) will be conducted before and after HBOT. Subjects will lay supine in a quiet dimly lit room for 20 min prior to injection of the radiopharmaceutical. Apart from administration of the injection by a physician, they will remainalone in the room during this period. Subjects will be asked to remain at rest for 10 min after the injection of the radiopharmaceutical to allow uptake of the radiopharmaceutical in the brain.

An injection of 925-1110 MBq (25-30 mCi) of technetium-99m ethyl cysteinate dimmer (Tc-99m-ECD) will be given into an arm vein through a previously placed intravenous cannula. SPECT imaging of the brain was performed, at 40-60 min post injection, with the subject’s head supported by a headrest, using a dual detector gamma camera (ECAM or Symbia T, Siemens Medical Systems) equipped with high resolution collimators. Data will be acquired in the step-and-shoot mode, using a 360 degree circular orbit, with the detectors of the gamma camera as close as possible to the subject’s head. The camera used for imaging will noted for each subject and the same camera will be used for the follow-up study. Data will be acquired using a 128׳128 image matrix in 3 degree steps of 20 seconds per step. Data will be reconstructed by iterative reconstruction with no filtering. The Chang method (*μ*=0.12/ cm) will be used for attenuation correction.

Intra subject visual analysis will be conducted using a process in which pre and post treatment studies are fused and normalized to pre-treatment whole brain activity.

Visual analysis will be carried out by two nuclear medicine physicians who compared the scans independently and grad them as either: 1=no change, 2=mild change and 3=significant change. Where, no change is assign when no visual difference is noted in the number or size of perfusion deficits, mild change is given when a reduced number of perfusion defects are noted or the size of the perfusion defects is reduced. Significant change should be attributed when a global perfusion increment is observe in addition to diminution of defect numbers or size. Differences in evaluation will be resolve after reviewing the images together. Scan visual interpretation will be carried out while blinded to any laboratory or clinical data.

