## Statistical Analysis

### Safety Analysis

AE's will be tabulated by treatment group, severity and relation to treatment.

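### One Yes/No relatedness rule covers both HBOT and study procedures, so events caused by the SPECT injection can be tabulated as treatment-related

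*Protocol*

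**What the plan says.** Assessment of Adverse Events (Protocol) has the investigator record, for each event, "severity, relationship to study drug or study procedures, outcome and action taken with study medication". One two-level scale follows: "The relationship to study drug therapy or study procedures should be assessed using the following definitions". The scale has two answers.

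- The negative answer, **No**, is given this meaning: "Evidence exists that the adverse event has an etiology other than the study drug or study procedures".
- **Yes** opens with: "A temporal relationship exists between the event onset and administration of the study drug or between the event and the study procedures". It adds a pharmacological or safety-profile plausibility condition that applies only when the suspected cause is the study drug.

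The same section asks for another explanation when an event is thought unrelated to the drug.

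Under Safety Analysis, events are to be "tabulated by treatment group, severity and relation to treatment". Study procedures are not mentioned there. The Safety Analysis Set keeps only subjects in whom study treatment was started. The Adverse Events section collects events from after the screening visit to the last day on study.

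The SPECT section describes a radiotracer that "will be given into an arm vein through a previously placed intravenous cannula". The Study protocol section makes this scan part of the evaluation for all patients. The treated group is evaluated at baseline and after HBOT. The cross group is evaluated at baseline, "after a 2 month control period of no treatment", and again after HBOT.

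**The concern.** The rule for recording relatedness and the table that reports it do not describe the same quantity. The rule asks whether the drug or a procedure caused the event; the table reports relation to treatment. No other relatedness variable is named, and nothing says how one becomes the other.

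Safety of HBOT in this population is a stated aim under Objectives, and relation to treatment is one of only three dimensions of the safety table. If imaging events fall into that column, a reader cannot tell harms of the chamber from harms of the scan. The problem arises when the data are captured, so a later analysis can undo only part of it.

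**Working it through.** The protocol states no figure to reproduce. The check sets its sections side by side.

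**Step 1. Classify a reaction caused by the SPECT injection or cannula.**
- No is unavailable, because the cause is a study procedure and No requires a cause other than the drug or the procedures.
- Yes fits on its opening condition, which a temporal link to a procedure satisfies. The drug-only plausibility condition does not apply.
- The case report form is not shown. Separate drug and procedure fields that used these same definitions would not cure the problem, because No in the drug field would still exclude a procedure-caused event.

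**Step 2. Carry the answer to the table.** Safety Analysis names relation to treatment only. If the recorded Yes feeds that column, the scan reaction appears as treatment-related. The text neither requires nor prevents this.

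**Step 3. Count the scans around first HBOT.** This assumes a scan at every evaluation, as the Study protocol section implies, and that baseline falls after the screening visit.

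| Group | Scans before first HBOT | Scans after HBOT | Total |
|---|---|---|---|
| Treated | 1 | 1 | 2 |
| Cross | 2 | 1 | 3 |
| One patient from each group (1:1) | 3 | 2 | 5 |

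The recorded onset date can show that events at 3 of the 5 scans preceded HBOT. It cannot separate the causes at the other 2. The cross group also has one more opportunity for a scan event than the treated group.

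**Step 4. Sensitivity only.** Let s be the chance that a scan causes a recorded event, and h the number of truly HBOT-related events per exposed patient. Both are assumptions. If every scan event were tabulated as related, and all patients completed the schedule:

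- overstatement, all scans = 5s / 2h
- overstatement left after pre-HBOT events are removed by date = 2s / 2h = s / h

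| s | h | All scans | After removal by date |
|---|---|---|---|
| 1% | 20% | 0.05 / 0.40 = 12.5% | 0.01 / 0.20 = 5% |
| 3% | 10% | 0.15 / 0.20 = 75% | 0.03 / 0.10 = 30% |
| 5% | 5% | 0.25 / 0.10 = 250% | 0.05 / 0.05 = 100% |

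These ratios do not depend on the sample size. The width of the range shows that the protocol supports no estimate. The last row deliberately pairs the highest assumed scan rate with the lowest assumed HBOT rate.

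**The case against.** The strongest reply is that relation to treatment in the table naturally means relation to HBOT, and that the mapping from form to table belongs in the SAP and form, which are not shown. The assessment section also contains judgements specific to the drug: the extra plausibility condition, and the request for another explanation when the drug is not suspected. Both help the investigator's reasoning. Neither creates a separate recorded answer, and the definition of No still rules out any procedure-caused event. That definition is stated in the protocol, so it is not a detail left to the SAP.

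The reply does defeat several stronger readings that a reader might infer:

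- **Pressure injuries qualify only as procedure events, and would vanish if the table meant drug only.** The exclusion "Chest pathology incompatible with pressure changes" shows that pressure hazards were foreseen. But Yes also admits the known adverse-event profile of the treatment, and the Study protocol section defines that treatment as oxygen at 2 ATA. Pressure is part of it.
- **The answer can never be split afterwards.** Onset dates are recorded, so events before the first session can be identified.
- **Patients who never receive HBOT are affected.** The Safety Analysis Set excludes them. Only early events in patients who later start HBOT are at issue.

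**Conclusion.** The point holds in a limited form. The protocol combines two causes in one relatedness rule, reports a single cause in the table, and does not connect them. SPECT events can therefore be counted as treatment-related. To say that they will be so counted goes further than the text, because the form and the table programming are not shown.

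The size cannot be estimated from the protocol, and the ratios above show sensitivity only. The scan counts assume imaging at every evaluation. The SPECT section itself speaks only of scans before and after HBOT; if the cross group had only two scans, the difference between groups would disappear but the classification problem would remain.

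This is a modest correction to safety reporting. It has no bearing on the efficacy analysis, alpha or the sample size.

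**What to change.** In Assessment of Adverse Events, replace the single judgement with two, each with its own definitions of Yes and No:

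- (a) related to the HBOT session, meaning the oxygen and pressure exposure;
- (b) related to other study procedures, such as the SPECT injection.

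Under Safety Analysis, state that relation to treatment is tabulated from (a), that (b) is shown on its own line, and that (a) is not applicable to events with onset before the patient's first HBOT session.

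The cost is one more field on the case report form, a short change to each of the two sections, and one extra judgement per event for the investigator. No visits, patients or procedures are added.

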***Serious Adverse Events***

**A** **serious adverse event** (SAE) is defined as follows:

Any adverse drug experience occurring at any dose that results in any of the following outcomes:

- Death;
- Life-threatening situation (subject is at **immediate** risk of death);
- In-patient hospitalization or prolongation of existing hospitalization (excluding those for study therapy or placement of an indwelling catheter, unless associated with other serious events);
- Persistent or significant disability/incapacity;
- Congenital anomaly/birth defect in the offspring of a subject who received study drug;

Other: medically significant events that may not result in death, be immediately life-threatening, or require hospitalization, may be considered a SAE when, based upon appropriate medical judgment, they may jeopardize the Subject and may require medical or surgical intervention to prevent one of the outcomes listed in this definition.

Examples of such events are:

- Intensive treatment in an emergency room
- Blood dyscrasias or convulsions that do not result in hospitalization
- Development of drug dependency or drug abuse

The investigator should notify the Institutional Review Board (IRB) or Independent Ethics Committee (IEC) as soon as is practical, of serious events in writing where this is required by local regulatory authorities, and in accordance with the local institutional policy.

